## Background

There is a high rate of psychological comorbidity in people with alcohol dependence [1,2]. This is of concern given that, during treatment, the time to relapse is shorter, the drop-out rate is increased, and long-term alcohol consumption is greater for those with comorbid major depression or anxiety disorder than for those with an alcohol use disorder (AUD) with no comorbid mental disorder [3-5]. In the Australian National Survey of Mental Health and Wellbeing, Teesson and colleagues [6] reported that 33% of more than 10,000 respondents with an AUD also suffered from an anxiety or mood disorder as defined by the *Diagnostic and Statistical Manual of Mental Health Disorders,* 4th ed. (DSM-IV). In addition, this subpopulation was significantly more disabled and used health services more frequently than those with AUD with no comorbid mental disorder [6]. Results from the large alcohol treatment trial Project MATCH (Matching Alcohol Treatment to Client Heterogeneity) highlight psychiatric comorbidity as a significant factor influencing treatment response for alcohol dependence [7]. Similarly, we have reported that, among alcohol-dependent patients, clinically significant levels of depression predicted poor response to alcohol treatment [8]. Unfortunately, however, the treatment of alcohol dependence and psychological disorders is often the responsibility of different services, and this may hinder the treatment process. Accordingly, there is a need for an effective integrated treatment for alcohol dependence and comorbid anxiety or depression in outpatient services.

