### Instruments

#### Baseline assessment

Baseline assessment will be of 40 minutes’ duration and will be conducted upon consent to enter the trial. Data will be gathered on demographics, long-term alcohol consumption, medical history of alcohol- and nonalcohol-related illness, drug abuse, age of onset, and family history of alcohol problems. Recent (past 30-day) alcohol consumption will also be assessed by the timeline follow-back (TLFB) method [28]. Severity of dependence will be assessed by the Obsessive-Compulsive Drinking Scale (OCDS) [29] and by the Alcohol Dependence Scale (ADS) [30]. Functional disability will be assessed by the Short-Form Health Survey (SF-12) [31]. Depression, anxiety, and stress levels will be measured by the Depression Anxiety Stress Scales (DASS) [32]. Motivation to change and perceived self-efficacy are likely to vary between individuals and be a determinant of treatment outcome; therefore, these will be assessed by the Stages of Change Readiness and Treatment Eagerness (SOCRATES) Scale [33] and the Alcohol Abstinence Self-Efficacy (AASE) Scale [34]. Sleep disturbance will be assessed by the Insomnia Severity Index (ISI) [35], and the psychological basis of insomnia will be assessed by the Glasgow Sleep Effort (GSES) Scale. History of other drug use will be determined by the Opiate Treatment Index (OTI) interviewer-conducted questionnaire. Blood samples will be taken for full blood count and liver function tests.

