### Outcome measures

Primary outcomes include time to consumption of any alcohol (lapse) as identified by self-reported alcohol consumption; time to relapse as ≥ 4 drinks for women, ≥ 6 drinks for men; amount of alcohol consumed (total abstinence and average consumption per drinking day). Secondary outcomes include improvement in depressive or anxiety symptoms (DASS) or alcohol dependence severity (ADS); biological markers of alcohol consumption at 6, 12, 16, and 24 weeks (carbohydrate-deficient transferrin, liver function, and mean corpuscular volume); episodes of alcohol-related harm (psychosocial, occupational, forensic, medical); and clinician-rated severity of anxiety and depression based on ADIS and HRSD.

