### Statistical analysis

The modified intention-to-treat principle will be used such that all subjects who attend the first intervention session will be analyzed [50]. The success of randomization will be tested by comparing baseline characteristics of the study groups with potentially confounding variables included as covariables. Analysis of variance will be used to compare continuous variables. Categorical variables will be compared via chi-square test. The effect of treatment on time-related outcome measures such as lapse and relapse will be analyzed by life-table survival analysis. Binary linear generalized estimating equations (GEE), with autoregressive correlation matrices, will be employed to determine differences between integrated care and usual care groups on change in anxiety or mood symptoms. A series of regression analyses will be performed to assess the role of symptomatic change in alcohol consumption and vice versa. Last-point carried forward or multiple imputation will be used to determine the scores of participants who drop out or are lost to follow-up. One previous study [9] with a similar design (N = 35) demonstrated that combined CBT treatment of alcohol dependence and comorbid depression significantly improved alcohol use outcomes with a moderate effect size. Power analysis has thus been performed such that a sample of 60 subjects (30 per group) has 80% power of detecting a moderate difference between the two arms of care on alcohol use outcomes at alpha = 0.05.

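### Time to lapse and time to relapse are tied to a life table, which takes covariates only by stratification; a pre-specified Cox model would use the SSRI stratum and predictors already measured

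*Protocol article*

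**What the plan says.** All places are in the protocol article.

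- **Outcome measures** makes lapse and relapse primary: "Primary outcomes include time to consumption of any alcohol (lapse) as identified by self-reported alcohol consumption", followed by time to relapse, total abstinence and average consumption per drinking day.
- **Statistical analysis** assigns one method to the two times: "The effect of treatment on time-related outcome measures such as lapse and relapse will be analyzed by life-table survival analysis".
- The same section mentions covariables once, in the sentence on checking whether randomization succeeded, by "comparing baseline characteristics of the study groups with potentially confounding variables included as covariables". Two general sentences follow: "Analysis of variance will be used to compare continuous variables" and "Categorical variables will be compared via chi-square test". They do not say whether they mean baseline variables, outcomes or both.
- Models are named for other purposes: GEE for change in anxiety or mood symptoms, and regressions for the link between symptom change and drinking.
- **Randomization and allocation concealment** stratifies by SSRI use. No method named for the drinking outcomes mentions that stratum.
- On predictors, **Baseline assessment** says "Motivation to change and perceived self-efficacy are likely to vary between individuals and be a determinant of treatment outcome", and **Background** reports that "clinically significant levels of depression predicted poor response to alcohol treatment". Table 2 places the self-efficacy and motivation scales at step 1, the Hamilton depression rating at step 2, and the DASS at both. All of these precede randomization.

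**The concern.** Symptom change, a secondary outcome, gets a regression-type model. The primary time-to-event outcomes get a method with no regression term. A life table can be stratified by a categorical factor such as SSRI use. With 60 patients, further stratification by a depression or self-efficacy score quickly leaves cells too thin to be useful.

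The covariable phrase adds uncertainty. If it refers to the outcome analyses, the named method has no practical way to carry a continuous covariable. If it refers only to the baseline check, no adjustment is planned for lapse and relapse, despite a stratified randomization and predictors that the authors themselves name. Either way the sentence needs work.

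At stake is precision in a small trial. Omitting a prognostic covariate from a time-to-event comparison pulls the hazard ratio toward 1 and lowers power.

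**Working it through.** **The plan's own figure.** The article claims 80% power with 30 per group for a moderate difference, without a number for moderate. Taking d = 0.5 as an assumption, two-sided power is Φ(0.5 × √(30/2) − 1.96) = Φ(1.936 − 1.960) = Φ(−0.024) = 49%. So the 80% is not reproduced at that value, and it cannot be confirmed without a stated effect. That is a separate matter. It matters here only because it shows there is little power to spare.

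**Inputs from the article.** 30 per arm; randomization at about week 3; last visit at week 24, so (24 − 3) × 7 = 147 days of follow-up.

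**Assumed inputs.** The article gives no event rate, hazard ratio or predictor strength. Both simulations use a true hazard ratio (HR) of 0.5 and one standardized predictor.
- Simulation A: exponential times over 147 days, 20% lapse-free under usual care, 25% random loss, 3,000 trials per setting.
- Simulation B: exponential times over 21 weeks, usual-care hazard 0.08 per week at the predictor's mean (exp(−0.08 × 21) = 19% lapse-free), no loss, about 40 events, 1,500 trials per setting.

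**Benchmark.** Schoenfeld's formula, power = Φ(|ln HR| × √(D/4) − 1.96), with D = 40 and HR 0.5 gives Φ(0.693 × 3.162 − 1.96) = Φ(0.232) = 59%. Simulation B with a non-prognostic covariate also gives 59%.

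**Power without and with the predictor in a Cox model.**

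| Predictor HR per SD | Simulation | Unadjusted | Adjusted | Gain (points) |
|---|---|---|---|---|
| 1.00 | B | 58.9% | 58.7% | about 0 |
| 1.50 | A | 47.3% | 51.5% | 4.2 |
| 1.65 (e^0.5) | B | 51.2% | 58.9% | 7.7 |
| 2.00 | A | 38.4% | 51.6% | 13.2 |
| 2.72 (e^1) | B | 33.2% | 54.5% | 21.3 |

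The Monte Carlo standard error of a single power figure is at most √(0.25/1500) = 1.3 points in B and √(0.25/3000) = 0.9 points in A. Type I error in A was 4.8 to 5.3% across the unadjusted and adjusted analyses.

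**Size of the estimate.** In B the median unadjusted HR is 0.50, 0.53 and 0.61 as predictor strength rises; the adjusted HR stays at 0.50. This is not bias in the usual sense. The unadjusted HR answers a population-average question and the adjusted HR a conditional one, so the power columns are the fairer comparison.

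**Grouping.** In a further simulation, grouping daily times into life-table intervals cost 0 to 4 points. The main loss comes from omitting a strong predictor, not from the intervals.

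**Abstinence.** Under A's assumptions, before loss, 30 × 0.20 = 6 usual-care patients and 30 × 0.20^0.5 = 30 × 0.447 = 13.4 integrated-care patients stay lapse-free. That is about 19 of 60, too few for more than one or two covariates in a logistic model.

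**The case against.** The strongest reply has four parts.

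1. *The comparison is valid without adjustment.* This stands. Randomization protects the test, and the simulated type I error agrees. The point is efficiency only.
2. *Predictor strength is assumed.* This also stands. The article gives no effect size for depression, motivation or self-efficacy. Everyone randomized has an anxiety or depressive diagnosis, which may narrow the range of depression severity and weaken it as a predictor. The smaller gains may be the realistic ones.
3. *Effect measures, intervals and covariate lists belong in the full protocol or SAP.* Their absence from an article is indeed no fault. But the article does more than stay silent: it fixes a method for the primary times, and an SAP written to match would inherit it.
4. *No contradiction is proved.* Correct, and stronger readings should be resisted:
   - A reader might infer that adjustment is promised and then made impossible. The covariable phrase sits in the baseline-comparison sentence, so that depends on how it is read.
   - A reader might infer that these methods give no effect size. Life tables give survival proportions with standard errors, and a 2×2 table gives a risk difference or ratio with an interval. The article only leaves open which will be reported.
   - A reader might infer that abstinence is assigned to chi-square. No sentence says so by name.
   - A reader might infer that the primary result shrinks to an unadjusted p-value. Average consumption per drinking day is also primary, and if analysis of variance is meant for outcomes, it gives mean differences and extends to covariables.

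**Conclusion.** The point holds as one of precision. For time to lapse and time to relapse the article fixes a method that uses covariates only through stratification, although a stratification factor and likely predictors are available before randomization.

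With 30 per arm and a true HR of 0.5, adjustment is worth about 4 to 8 points of power for a predictor HR of 1.5 to 1.65 per SD, 13 to 21 points at 2.0 to 2.7, and nothing at 1.0. These figures rest on assumed event rates, exponential times and predictor strengths. The two simulations agree in direction. The change is worth making, but the trial's validity does not depend on it.

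**What to change.** 1. **Lapse and relapse.** Analyze both times from randomization with a Cox model containing treatment, the SSRI stratum and one or two covariates fixed in advance, for example step-2 depression severity and baseline self-efficacy. Do not choose covariates by baseline significance tests. Report the hazard ratio with 95% CI alongside life-table or Kaplan-Meier curves.
2. **Covariable sentence.** Say plainly whether it concerns the outcome analyses, and whether the ANOVA and chi-square sentences refer to baseline variables, outcomes or both.
3. **Total abstinence.** If chi-square is intended, replace it with logistic regression containing treatment, the SSRI stratum and at most one further covariate. Report an odds ratio, or a risk difference obtained by standardizing over the covariates, with 95% CI.

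The cost is a change of wording; every variable is already collected. In return, proportional hazards must be checked, and the covariate list must stay short with about 40 events and perhaps 19 abstinent patients.

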## Methods

### Procedure

The flow of participants is outlined in Figure 1. The first phase of the study is to establish a stabilization period from alcohol for three weeks before entering the randomization step of the study. During the stabilization period, participants will have the option of pharmacotherapy using naltrexone (50 mg, 1 tablet daily), acamprosate (333 mg, 2 tablets 3 times daily, reduced to 4 per day for women weighing < 65 kg), or a combination of the two as medically prescribed based on physician judgment and participant preference. After a three- to four-week stabilization period, patients will undergo complete formal assessment for anxiety and depression. Those with a diagnosis of anxiety or depressive disorder, regardless of drinking outcome, will be offered the next step of care. The remaining participants will be monitored for a further nine weeks while receiving alcohol pharmacotherapy and/or usual counseling care. Patients to undergo the next phase will also continue to receive further alcohol pharmacotherapy as medically prescribed but will be randomized to one of two treatment groups: 1) integrated intervention for comorbid alcohol, anxiety, and/or depression, or 2) usual counseling care. Follow-up appointments will then be scheduled at weeks 12, 16, and 24 as described below.

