### Step 2: inclusion and exclusion criteria for randomization

Inclusion criteria for randomization include abstinence and/or clinically significant reduction in alcohol use per clinician judgment, resolution of any clinically evident alcohol withdrawal as indicated by CIWA-Ar results, and case formulation and diagnosis for anxiety or depression. Exclusion criteria include alcohol consumption at baseline levels and resolution of clinically evident anxiety or depression as assessed by the case formulation (see below). These patients will be offered further treatment as appropriate within the service and will continue to be monitored.

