**Table 2 T2:** Schedule of assessments

**Measure**	**Schedule**
Mini Social Phobia Inventory (Mini-SPIN)	Intake screening
Kessler Psychological Distress Scale (K10)	Intake screening
Comorbidity Suspicion Checklist (CSC)	Baseline (step 1*)
DSM-IV assessed dependence	Baseline (step 1)
Alcohol Dependence Scale (ADS)	Baseline (step 1), Weeks 12, 16, 24
Obsessive Compulsive Drinking Scale (OCDS)	Baseline (step 1), Weeks 12, 16, 24
Stages of Change Readiness and Treatment Eagerness (SOCRATES) Scale	Baseline (step 1), Weeks 12, 16, 24
Alcohol Abstinence Self-Efficacy (AASE)	Baseline (step 1), Week 12, 16, 24
Short-Form Health Survey (SF-12)	Baseline (step 1), Week 12, 16, 24
Depression Anxiety Stress Scale (DASS)	Baseline, Week 3 (step 2**), 12, 16, 24
Insomnia Severity Index (ISI)	Baseline, Week 3 (step 2), 12, 16, 24
Glasgow Sleep Effort Scale (GSES)	Baseline, Week 3 (step 2), 12, 16, 24
Timeline Follow-back (TLFB)	Baseline, Week 3 (step 2), 12, 16, 24
Anxiety Disorders Interview Schedule (ADIS)	Week 3 (step 2), Week 16
Hamilton Rating Scale for Depression (HRSD)	Week 3 (step 2), Week 16

*Step 1 = week 0 preceding three-week alcohol stabilization phase.

**Step 2 = formal diagnosis for depression and/or anxiety disorder preceding randomization to usual care or integrated care.

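### Last-point carried forward should be dropped: it would fix early drop-outs at their entry state, low in drinking and high in symptoms

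*Protocol article*

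**What the plan says.** The missing-data rule is one sentence in Statistical analysis: "Last-point carried forward or multiple imputation will be used to determine the scores of participants who drop out or are lost to follow-up". The two methods stand as equal alternatives. The same section keeps in the analysis everyone who attends the first intervention session, so a patient who leaves soon afterwards still needs a value. It sends lapse and relapse times to life-table survival analysis.

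Entry to the randomized phase is set out under Step 2: "Inclusion criteria for randomization include abstinence and/or clinically significant reduction in alcohol use per clinician judgment". The same paragraph adds: "Exclusion criteria include alcohol consumption at baseline levels". The Procedure section reads differently: "Those with a diagnosis of anxiety or depressive disorder, regardless of drinking outcome, will be offered the next step of care". Randomization also requires a diagnosis of anxiety or depression.

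Table 2 schedules the timeline follow-back (TLFB) and the DASS at "Baseline, Week 3 (step 2), 12, 16, 24". It schedules ADIS and HRSD only at week 3 and week 16. It lists the ADS at "Baseline (step 1), Weeks 12, 16, 24", whereas the section on formal diagnosis also has the ADS given at step 2.

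Under Outcome measures, total abstinence and average consumption per drinking day are primary, beside time to lapse and time to relapse. DASS, ADS, ADIS and HRSD are secondary.

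**The concern.** LOCF assumes that nothing changes after the last contact. Here the last contact before treatment is a selected moment: drinking has just fallen and the mood or anxiety disorder is still present. For a patient lost between week 3 and week 12, LOCF reports that moment as the week 24 result. In a relapsing condition this is likely to understate drinking, and if symptoms generally ease it overstates them.

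Three things are at stake:

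- Filled-in values enter the analysis as if measured, so the standard error carries nothing for the uncertainty of filling them in.
- If both arms lose the same share, a real treatment effect is diluted.
- If the arms lose different shares, the comparison is biased, in opposite directions for drinking and for symptoms.

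The planned regressions of symptom change on drinking, and the reverse, would also include drop-outs artificially held at low drinking and high symptoms.

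**Working it through.** **Inputs from the article.** 30 patients per group, alpha 0.05, and the visit schedule in Table 2. The article gives no drop-out rate, abstinence rate or standard deviation, so it has no figure of its own to reproduce on this point. All rates below are assumptions.

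**Which outcomes LOCF can reach**

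| Outcome | Value carried if lost before week 12 | Likely direction |
|---|---|---|
| Time to lapse, time to relapse | none (life table) | not affected |
| Total abstinence, drinks per drinking day | week 3 TLFB, reduced drinking | flatters drop-outs if they drink more after leaving |
| DASS | week 3, symptomatic | penalizes drop-outs if patients generally improve |
| HRSD, ADIS | week 3, symptomatic (also for anyone missing week 16) | as DASS |
| ADS | week 0 by Table 2, or step 2 by the text | depends on which is right |

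**Abstinence, no true effect.** Let p_L be the share of drop-outs abstinent at last contact, p_T the share of them truly abstinent at week 24, and d_A and d_B the drop-out proportions. Each arm's rate is shifted by d × (p_L − p_T), so

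spurious difference = (p_L − p_T) × (d_A − d_B).

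- Equal drop-out: (p_L − p_T) × 0 = 0.
- p_L 0.60, p_T 0.30, drop-out gap 0.10: 0.30 × 0.10 = 0.03.
- p_L 0.65, p_T 0.20, drop-out 0.30 v 0.15: 0.45 × 0.15 = 0.0675.
- p_L 0.80, p_T 0.20, drop-out gap 0.15: 0.60 × 0.15 = 0.09.

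For scale, with 30 per arm and 30% abstinent, the standard error of the difference is √(2 × 0.30 × 0.70 / 30) = √0.014 = 0.118, or about 12 points.

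**Continuous drinking outcome, no true effect.** Let m be the mean worsening after entry, in SD units, and let all drop-outs leave before week 12. The bias is m × (d_A − d_B). With completer SD 1 and carried-value SD 0.5, each arm's variance is (1 − d) + 0.25d + d(1 − d)m², and the standard error is √((v_A + v_B)/30).

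Example with m = 1 and drop-out 0.40 v 0.20: the bias is 0.20; v_A = 0.60 + 0.10 + 0.24 = 0.94; v_B = 0.80 + 0.05 + 0.16 = 1.01; the standard error is √(1.95/30) = 0.255; the two-sided rejection rate is 12.3%.

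| Drop-out | Bias (SD), m = 0.5 to 1.5 | Type I error |
|---|---|---|
| 20% v 20% | 0 | 5.0% |
| 30% v 20% | 0.05 to 0.15 | 5.5% to 8.2% |
| 40% v 20% | 0.10 to 0.30 | 7.1% to 18.3% |

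**Dilution with equal drop-out.** If drop-outs carry entry values that do not differ by arm, a true effect of 0.5 SD becomes 0.5 × (1 − d): 0.45 at 10% drop-out and 0.35 at 30%.

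**The case against.** Several stronger readings are tempting, and the article does not support them.

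- **LOCF rewards the arm that loses more patients.** A reader might infer this for the trial as a whole. It can hold for drinking amount and abstinence only. The sentence speaks of scores and follows the analyses of anxiety and mood symptoms, where the entry value is the bad state and the direction tends to reverse. Two primary outcomes are untouched.
- **Drop-outs are given their best drinking state.** Patients lost after week 12 or 16 carry that visit's value, which may already show relapse. Entry allows reduced drinking, not only abstinence, and Procedure says drinking does not matter for entry. If the 30-day recall window applies at week 3, it reaches back 30 − 21 = 9 days before enrolment. Enrolment requires as few as three abstinent days, so up to 6 of those days could include earlier drinking.
- **The article itself predicts unequal drop-out.** Background does say that "the drop-out rate is increased, and long-term alcohol consumption is greater for those with comorbid major depression or anxiety disorder". That compares comorbid with non-comorbid patients, and everyone randomized here is comorbid. It supports expecting drop-out and relapse, not a gap between arms. The arms do differ in what they ask of patients, so a gap is possible, in either direction.
- **The choice between methods can be made after seeing both results.** The article does not say when the choice is made. It is a condensed account and the SAP is not shown, so the open choice and the absence of a named sensitivity analysis are weak grounds.

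What remains is that the article names LOCF as an acceptable method, and for the outcomes it reaches the design gives good reason not to use it.

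**Conclusion.** The concern holds in a limited form. LOCF is permitted, though not certain to be used, and it is a poor method for the drinking outcomes that are not times to event and for the symptom scores. The two kinds of outcome would tend to be biased in opposite directions.

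For abstinence, the spurious difference between arms is 0 with equal drop-out and about 3 to 9 percentage points with drop-out gaps of 10 to 15 points. This rests on assumed abstinence of 60% to 80% at last contact and 20% to 30% in truth at week 24, with every drop-out carrying the entry value. Later losses would probably make it smaller. Against a standard error of about 12 points this is a material shift, but it is conditional on a drop-out gap that the article neither states nor implies. Two consequences do not need such a gap: a true effect is diluted, and filled-in values are treated as observed.

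The argument about drinking is strongest under the Step 2 criteria, which the statement in Procedure contradicts.

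**What to change.** Delete LOCF and name one primary method: multiple imputation under missing at random, already permitted, or a likelihood-based mixed model for the continuous scores. Keep the imputation model small: arm, SSRI stratum, step-2 value and the observed values of the same outcome. A large model fitted within each arm would not be workable. Three DASS scores and one TLFB value at five visits, plus the stratum, make 3 × 5 + 5 + 1 = 21 variables. At an assumed 30% drop-out, an arm has 30 × 0.70 = 21 completers.

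Add one sensitivity analysis for the drinking outcomes: missing counted as relapse, or a delta-adjusted imputation. State that the time-to-event outcomes stay with the life-table analysis.

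Reconcile Procedure with the Step 2 criteria on drinking at entry, and Table 2 with the formal-diagnosis section on whether the ADS is given at step 2. The imputation model needs to know what the step-2 value is.

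The cost is revised wording, a little more analysis work and somewhat wider intervals. No data collection changes unless the ADS reconciliation adds a step-2 measurement.

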To date, research has usually assessed different psychosocial methods or pharmacological treatments targeted at alcohol dependence and psychological disorders separately. The focus has rarely been on concurrent treatment for both conditions. Regarding alcohol dependence and comorbid depression, there have been only two psychosocial intervention trials. Brown et al. [9] observed in 35 inpatients that adding CBT for depression versus relaxation training to standard partial hospital alcohol treatment was more effective in reducing depressive symptoms and some drinking outcomes than treatment for the alcohol problem only. They also observed that decreases in somatic depressive symptoms mediated the relationship between treatment condition and drinking outcomes. However, in a follow-up larger clinical trial, Brown et al. [10] found no significant differences on alcohol use outcomes and inconsistent effects on symptoms of depression. In both these studies, the interventions for depression and alcohol were not integrated, and the alcohol psychoeducational intervention was group-delivered only during the initial hospital stay.

There have been some studies investigating concurrent, but not integrated, treatments for alcohol dependence and anxiety disorders. Two studies found little beneficial effect from concurrent treatment for alcohol dependence and anxiety disorders (panic disorder and social phobia) [11,12]. However, in both studies, limited success may have been due, in part, to an inability to differentiate alcohol-related anxiety from non-alcohol–related symptoms at baseline assessment. Patients were either in withdrawal or not necessarily abstinent at the time of assessment, such that that anxiety symptoms resulting from alcohol withdrawal may have confounded the initial diagnoses. In many cases, symptoms of depression and anxiety resolve with abstinence so that further treatment is not required. However, in other cases where abstinence is achieved, these symptoms persist or worsen. To this degree, the stepped-care model entails assessing the outcome of primary treatment and systematically offering a secondary treatment where indicated and thus has the potential to provide a clearly structured, logical, and economical treatment [13-15].

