### Participants

A total of 100 patients will be recruited from inpatients and outpatients of participating hospitals via flyers and community advertisements at local general practice offices, in newspapers, and on the Sydney Alcohol Treatment Group website. Conservatively assuming that 40% of respondents will not be eligible for randomization at step 2 following diagnosis for depression or anxiety disorder, we anticipate that 60 patients will be randomized to one of the two groups. Participant time and travel expenses will be reimbursed at follow-up assessments. The trial will be conducted at the Drug Health Services outpatient clinic of the Royal Prince Alfred Hospital, NSW, Australia. Ethics approval for the study has been granted by The Sydney Local Health District Ethics Review Committee (X05-0275).

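### The claimed 80% power for a moderate difference is wrong: 30 per group give about 48% at d = 0.5, before any loss

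*Protocol article*

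**What the plan says.** The power statement is the last sentence of the protocol article's Statistical analysis section. For the alcohol outcomes, at alpha 0.05, it makes this claim: "a sample of 60 subjects (30 per group) has 80% power of detecting a moderate difference between the two arms of care". The size of the effect is given only as a label. It is taken from one earlier trial with 35 patients, described there as similar in design, which is said to have "significantly improved alcohol use outcomes with a moderate effect size". No standardized difference, standard deviation, event rate, hazard ratio or sidedness is given, and the sentence does not say which alcohol outcome it refers to.

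Three other places bear on it:

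- **Participants:** of 100 recruited, 40% are expected to be ineligible at step 2, so "we anticipate that 60 patients will be randomized to one of the two groups". The allowance is applied before randomization and none is made after it.
- **Background, on drop-out:** in this population "the drop-out rate is increased, and long-term alcohol consumption is greater for those with comorbid major depression or anxiety disorder".
- **Background, on the source trial:** the 35 patients were inpatients and the treatments were not integrated. The larger follow-up trial by the same group "found no significant differences on alcohol use outcomes and inconsistent effects on symptoms of depression".

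For analysis, the Statistical analysis section names analysis of variance for continuous variables, chi-square tests for categorical ones and life-table methods for lapse and relapse. GEE models are tied to anxiety and mood symptoms only.

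**The concern.** Sample size, allocation, alpha, power and an effect label are all stated, so the claim can be checked. Anyone who has sized a two-arm trial will recall that a standardized difference of 0.5 needs a little over 60 patients per group, not 30.

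What is at stake is how the result is read. A stated power of 80% tells readers that a true moderate effect would be missed one time in five. If the real figure is near 48%, it would be missed about half the time even with complete data. A non-significant result would then be given more weight against the intervention than the design can bear. The Discussion does not correct this: its caveat about power covers only the study of processes and mechanisms, not the alcohol outcomes.

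**Working it through.** **Inputs from the article:** 30 per group; alpha 0.05; power 80%; effect described as moderate.

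**Assumptions:** two-sided test as base case, one-sided also shown; moderate means d = 0.5 as base case, other conventions also shown; loss rates of 10%, 20% and 30% are illustrative, since the article gives none.

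**1. What effect does the stated 80% correspond to?** Normal approximation:

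d = (1.960 + 0.8416) × √(2/30) = 2.8016 × 0.2582 = 0.72

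The noncentral t distribution gives d = 0.736 two-sided and 0.65 one-sided. The stated figure is therefore recovered only at an effect well above 0.5.

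**2. Power at d = 0.5.** Normal approximation:

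Φ(0.5 × √(30/2) − 1.960) = Φ(1.936 − 1.960) = Φ(−0.024) = 0.49

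Noncentral t: 0.478 two-sided, 0.606 one-sided. Two-group ANOVA with f = 0.25 is the same test and gives 0.478.

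**3. Sample size for 80% at d = 0.5.**

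n = 2 × 2.8016² / 0.5² = 62.8 per group

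The t distribution gives 63.8, so 64 per group (128 in total) before loss.

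**4. Sensitivity to d** (30 per group, two-sided t):

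| d | Power |
|---|---|
| 0.4 | 33% |
| 0.5 | 48% |
| 0.6 | 63% |
| 0.7 | 76% |
| 0.74 | 80% |
| 0.8 | 86% |

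**5. Loss after randomization** (two-sided t):

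| Assumed loss | n per group | Power at d = 0.5 | d for 80% power |
|---|---|---|---|
| none | 30 | 48% | 0.74 |
| 10% | 27 | 44% | 0.78 |
| 20% | 24 | 40% | 0.83 |
| 30% | 21 | 35% | 0.89 |

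**6. The other tests the article names.**

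- Chi-square, w = 0.3, N = 60: 64%. With Cohen's h = 0.5 for two proportions: 49%. Power of about 80% on proportions needs a difference of roughly 35 percentage points (20% against 55% gives 82%; 40% against 75% gives 80%).
- Time to event, Schoenfeld's formula with equal arms and D events: detectable HR = exp(−2.8016 × 2/√D). For D = 60, exp(−0.723) = 0.485; for D = 45, exp(−0.835) = 0.434. With all 60 having an event, a hazard ratio of 0.6 has 51% power.

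**7. Readings that come nearer to 80%.**

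- Regression f² = 0.15, N = 60: 84%. In a comparison of two equal groups f = d/2, so d = 2 × √0.15 = 0.77.
- Significance in the source trial: with N = 35, a simple two-group test needs an observed d of at least 0.69. With 30 per group, power at d = 0.69 is about 75%.
- Baseline-adjusted mean of three follow-ups at d = 0.5: 82% to 93% for correlations from 0.2 to 0.7. Adjusting a single follow-up for baseline reaches 80% only if the correlation is about 0.73.

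**The case against.** The strongest reply is that the article never says d = 0.5. Its moderate effect comes from a trial not shown here, and if that trial was significant with 35 patients by a simple two-group test, its observed effect was at least about 0.69. Under one standard convention (f² = 0.15) the sample does give more than 80%. A baseline-adjusted repeated-measures analysis could also get there, and drinking by timeline follow-back is scheduled at baseline and at weeks 3, 12, 16 and 24. The article is a condensed account, so the full calculation may lie elsewhere. The loss rates are not from the article, and nothing in it says how a null result would be read.

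Part of this stands. The value 0.5 is an assumption, the loss scenarios are illustrations, and the misreading of a null result is an inference. The suitability of the 35-patient trial is a side issue: the Background openly reports its setting and the null larger trial, and the arithmetic does not depend on it.

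The figure is still not rescued. Taking 0.69 as the effect gives about 75%. The f² convention passes only because, with two arms, it means d = 0.77, which few readers would call moderate. No repeated-measures or covariate-based calculation is stated for alcohol outcomes; GEE is named only for symptoms, and a mean over follow-ups does not apply in that form to lapse, relapse or total abstinence. If such a model lay behind the 80%, the sentence would still have to say so.

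**Conclusion.** The power statement is wrong as written. For a two-sided comparison of two groups of 30, a moderate effect of d = 0.5 has about 48% power (61% one-sided), and 80% is reached only at d of about 0.74. The shortfall does not hinge on the choice of test: the chi-square version gives 64% at w = 0.3, and the survival version needs a hazard ratio of about 0.49 with every patient relapsing.

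The conclusion rests on the conventional meaning of moderate and on a single two-group comparison, which is what the article describes for these outcomes. The 48% assumes that all 60 patients are analyzed. The modified intention-to-treat rule, which keeps only those who attend the first session, and the drop-out the article itself expects can only lower it. This should be corrected, because it is the only justification given for the sample size on the primary outcomes.

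**What to change.** Keep N and restate the figure. Suggested text: *With 30 patients per group, a two-sided test at alpha 0.05 has 80% power for a standardized difference of 0.74 (0.83 if 20% are lost), or for a relapse hazard ratio of about 0.49 if all patients relapse (0.43 if 45 do). Power for a standardized difference of 0.5 is about 48% (40% if 20% are lost).* The 20% should be labelled as an assumption or replaced by the sponsor's own estimate.

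The sentence should also name the alcohol outcome, test and sidedness it refers to. If a repeated-measures or baseline-adjusted model was used, its correlation should be given and the figure recomputed.

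Two lesser changes would help:

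- Remove the step from the single 35-patient trial to 80% power, or cite the larger null trial beside it.
- Commit to reporting effect estimates with 95% confidence intervals, so that a non-significant result is not read as no effect.

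The cost is wording in the protocol or SAP. Recruitment, conduct and patient burden do not change; the stated power becomes less favourable. Keeping the 80% claim at d = 0.5 would instead need about 64 per group plus an allowance for loss, more than double the planned number.
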